**Discussion:**

This RCT aims to provide robust clinical evidence on the perioperative and long-term outcomes of vNOTES versus TU-LESS for tubal ectopic pregnancy, focusing on key reproductive and surgical outcomes. The study seeks to refine patient selection criteria and contribute to guideline development for gynecologic vNOTES.

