### Study population

#### Sample size calculation

Sample size estimation was based on the NOTABLE cohort study [24]. Previous studies report a conversion rate for vNOTES in tubal ectopic pregnancies between 1.83% and 3.07%, suggesting a surgical success rate of approximately 95%.^34,35^A one-sided non-inferiority test was used to determine the sample size, assuming that vNOTES would remain a preferred option despite a potential 15% lower success rate compared to TU-LESS, which results in visible scarring. To achieve 85% power for non-inferiority with a 95% expected success rate in both groups, a total of 54 cases were required. Accounting for an anticipated 20% dropout rate, the final sample size was set at 72 participants, with 36 per group.

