### Statistical analysis

Statistical analyses will be conducted using SPSS (Version 25.0) and R. Continuous variables will be analyzed using t-tests or Mann–Whitney tests, with results presented as means ± standard deviations for normally distributed data and medians with interquartile ranges for non-normally distributed data. Categorical variables will be analyzed using chi-square or Fisher’s exact tests. To mitigate bias, statistical techniques such as propensity score matching (PSM), stratification, multivariate analysis, Cox regression, and generalized estimating equations (GEE) will be employed as necessary. A binary logistic regression analysis will also be conducted to assess the risk factors for surgical conversion, incorporating variables that demonstrate a significant statistical difference in the univariate comparisons. Statistical significance will be set at *p* < 0.05.

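### The planned logistic regression for risk factors of conversion, with predictors screened by univariate p-values, would rest on too few conversions (about 3.6 expected in 72 patients) to estimate even one predictor reliably

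*Protocol article*

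**What the plan says.** Under Statistical analysis, the protocol article states: "A binary logistic regression analysis will also be conducted to assess the risk factors for surgical conversion". Predictors enter by a screening rule: "incorporating variables that demonstrate a significant statistical difference in the univariate comparisons". The threshold is given in the same section: "Statistical significance will be set at *p* < 0.05". The techniques listed just before the regression are to be used as necessary; the regression carries no such condition.

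The Sample size calculation section supplies the event rates. It cites a "conversion rate for vNOTES in tubal ectopic pregnancies between 1.83% and 3.07" per cent. The calculation itself is set up "To achieve 85% power for non-inferiority with a 95% expected success rate in both groups", which means 5% conversion per arm. The final size is 72, with 36 per group.

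The article attaches no minimum number of conversions, no cap on predictors, no sparse-data method and no exploratory label to this regression.

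**The concern.** The information in a logistic regression is governed by the number of events, and conversion is planned to be rare. Screening many candidates against a handful of events adds a second problem. The factors that pass tend to be those where one or two patients happen to line up, and the odds ratios that follow are inflated or infinite.

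Conversion is the complement of the primary short-term outcome (completion by the allocated technique). A table of its risk factors from a randomised trial could therefore be read as guidance on who is unsuitable for vNOTES. If it rested on two or three patients, that reading would be unsafe.

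This is not a detail that can be left to a statistical analysis plan, because the article itself fixes both the model and the entry rule.

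**Working it through.** **Inputs.** N = 72, 36 per arm, and conversion of 5% in both arms (1 − 0.95), all from Sample size calculation. The range 1.83% to 3.07% comes from the same section but is for vNOTES only; using it for both arms is my assumption. The article states no expected number of conversions, so there is no figure of its own to reproduce. I take 72 as given. Whether 72 follows from the stated power inputs is a separate question that does not affect this point.

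**Step 1: expected conversions and exact binomial probabilities.** Expected = N × rate: 72 × 0.0183 = 1.32; 72 × 0.0307 = 2.21; 72 × 0.05 = 3.60.

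| Rate, both arms | Expected | P(0) | P(≤1) | P(≤4) | P(≥5) |
|---|---|---|---|---|---|
| 1.83% | 1.32 | 0.265 | 0.620 | 0.990 | 0.010 |
| 3.07% | 2.21 | 0.106 | 0.347 | 0.929 | 0.071 |
| 5% | 3.60 | 0.025 | 0.119 | 0.708 | 0.292 |

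These are the favourable figures, with all 72 analysed. With 54 analysed, the expected counts are 0.99, 1.66 and 2.70.

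**Step 2: less favourable surgery, hence more events.** At 10% conversion in both arms, 72 × 0.10 = 7.2. With vNOTES at the non-inferiority boundary (20% conversion against 5%), 36 × 0.20 + 36 × 0.05 = 7.2 + 1.8 = 9.0. Several predictors cannot be supported even there.

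**Step 3: what the screening rule lets through.**
- *Balanced binary factor (36/36, such as treatment arm), Fisher's exact test, every conversion on one side.* Four events: 2 × C(36,4)/C(72,4) = 0.11. Five events: 2 × C(36,5)/C(72,5) = 0.054. Six events: 0.025. With five or fewer conversions such a factor cannot pass, however strong its effect.
- *Uncommon factor (11 of 72 exposed, chosen for illustration), two conversions, both exposed.* C(11,2)/C(72,2) = 55/2556 = 0.022. It passes on two patients, leaves an empty cell and has no finite odds ratio.
- *Continuous factor, one conversion, exact Mann–Whitney test without ties.* The smallest two-sided p is 2/72 = 0.028, when the converted patient has the highest or lowest value. The next is 4/72 = 0.056. The factor can pass only at the extreme, and that is complete separation.

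**Step 4: null simulation of the whole procedure.** There were 1,500 trials per rate, N = 72, and 12 candidates unrelated to conversion. Selection was at p < 0.05 by Mann–Whitney or Fisher's test, followed by a linear-programming check for separation. The number of candidates and their form (six continuous; six binary with prevalence 15% to 50%) are assumptions. Baseline information lists about 13 variables, but the article does not say that these are the candidates.

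| Rate | No conversions | Conversions, nothing selected | At least one factor selected | Separated, of those selected |
|---|---|---|---|---|
| 1.83% | 26% | 57% | 17% | 45% |
| 3.07% | 10% | 67% | 23% | 31% |
| 5% | 3% | 67% | 30% | 23% |

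No model arises in 26 + 57 = 83%, 10 + 67 = 77% and 3 + 67 = 70% of trials. A model with finite estimates arises in 0.17 × 0.55 = 9%, 0.23 × 0.69 = 16% and 0.30 × 0.77 = 23%, although no candidate has any effect.

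**The case against.** The strongest defence is that the analysis is ancillary and partly limits itself. If nothing passes the screen, no model is fitted, and under the null simulation that is the usual outcome. The article also already plans a detailed description of converted cases, and its Discussion concedes that the sample may be too small for rare complications. All of this is fair, and it keeps the point away from the trial's main result. It does not rescue the regression: the concession is not applied to conversion, and the cases in which a model does appear are those most likely to mislead.

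Four stronger readings are tempting, and the documents do not support them.

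- *The model cannot be estimated at all.* With three or four conversions a one-predictor model can return finite values, and in the simulation most models with a selected factor did. The defect is unreliability.
- *Any factor it names would be noise.* The simulation held only noise candidates, so it gives a false-selection rate under the null. It does not give the chance that a named factor is false. A real effect and a chance one could not be told apart; that is as far as the evidence goes.
- *The trial means to refine patient selection from this regression.* The Abstract's Discussion paragraph says "The study seeks to refine patient selection criteria", as an aim of the whole study. Nothing ties it to this model.
- *There will be at most four conversions.* The figures 1.3 to 3.6 are expected values. At 5%, five or more have a 29% chance.

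Using the vNOTES range for both arms is also an assumption. The Background reports slightly higher conversion with vNOTES than with TU-LESS, so this probably does not understate the count. The 5% figure, which the plan itself applies to both arms, is enough for the conclusion.

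**Conclusion.** The point holds in this form: the article fixes a regression and a univariate entry rule for an outcome expected in about 3.6 of 72 patients at its own planning rate, or in 1.3 to 2.2 if the vNOTES range applies to both arms. That cannot support reliable estimation of one predictor, and still less of several. The event counts need only the article's rates and N. The selection and separation percentages also depend on the assumed candidate set and should be read as indicative. The matter deserves correction before analysis, but it is secondary: the comparison of completion rates does not depend on it.

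**What to change.** In Statistical analysis, remove the univariate screening and the multivariable logistic regression for conversion. In their place:

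- report the number and proportion of conversions per arm with exact 95% confidence limits;
- give the case-by-case description already promised under Primary short-term outcome (reason, technique converted to, complications and their severity), with the complications, not the conversions, graded by Clavien–Dindo as under Secondary short-term outcomes.

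If the investigators want to keep a model, limit it to one predictor named before the data are seen, fit it by Firth-penalised or exact logistic regression, and label it exploratory.

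The change is to wording only and needs no extra data or patients. The price is that the trial can claim no table of risk factors for conversion.

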## Discussion

Tubal ectopic pregnancy poses a significant risk to maternal health and remains a leading cause of early pregnancy morbidity. Minimally invasive laparoscopic techniques are increasingly preferred for its management [2, 42]. Given its multiple advantages in treating benign gynecologic conditions, vNOTES has gained popularity among gynecologic endoscopic specialists [18]. Several retrospective studies indicate that vNOTES for tubal ectopic pregnancy and other benign gynecologic conditions, including emergency cases, is associated with reduced perioperative complications, superior cosmetic outcomes, decreased postoperative pain, and a faster recovery compared to conventional laparoscopic techniques [22, 34, 35, 43–45]. However, the lack of RCT design, comprehensive long-term follow-up data, and concerns regarding the financial burden of vNOTES may limit its widespread adoption [14, 15, 29]. 

The present study aims to compare vNOTES and TU-LESS due to their shared minimally invasive nature and similar clinical indications. TU-LESS has been increasingly adopted as an alternative to CL and MPL in benign gynecologic disease with surgical indications, making it a relevant comparator in the context of minimally invasive gynecologic surgery. At our institution, vNOTES and TU-LESS are preferred over CL and MPL due to their aesthetic and other advantages. Additionally, the economic costs of these surgical techniques do not differ significantly. Most patients opt for either vNOTES or TU-LESS, with the number of patients choosing vNOTES being approximately twice that of TU-LESS. A similar trend has also been observed in other countries with distinct cultural backgrounds compared to China [17]. Due to the greater invasiveness of CL, it is primarily reserved for intraoperative conversion in cases where severe complications prevent the completion of vNOTES or TU-LESS as initially planned. Moreover, previous studies have extensively compared MPL with vNOTES or TU-LESS [43, 45, 46]. For these reasons, our study, as well as other RCTs in the field of minimally invasive gynecologic surgery, aims to address a gap in the literature by specifically focusing on the comparison between vNOTES and TU-LESS rather than other surgical methods [23, 24, 32, 33, 47]. 

Patient perceptions of vNOTES have been extensively explored, with primary concerns relating to the necessity of culdotomy and its potential effects on incisional complications, sexual function, pregnancy, and vaginal delivery [48–50]. A retrospective study of 76 patients with a median follow-up of 77 months found no significant impact of hybrid-NOTES on pregnancy outcomes or delivery mode [51]. However, this study primarily involved transvaginal specimen retrieval rather than full vNOTES procedures. A more recent study reported that most women undergoing vNOTES achieved normal pregnancy and vaginal delivery, but the small sample size (*n* = 9) limits its statistical power and generalizability [28]. A prospective cohort study comparing the perioperative outcomes of vNOTES and TU-LESS hysterectomy involving 192 patients also found that the vNOTES group demonstrated several advantages over the TULESS group, including shorter operative time, faster postoperative recovery, reduced hospital stay, greater minimally invasive benefits, and improved cosmetic outcomes. However, intraoperative blood loss was greater in the vNOTES group [52]. While some RCTs comparing vNOTES and TU-LESS have been initiated [23, 24, 33], their follow-up duration and scope remain limited. Additionally, RCTs assessing the impact of vNOTES on sexual function have largely focused on non-gynecologic applications in non-Chinese populations, with few employing a single-blind RCT design [53–55]. 

Another key aspect of the vNOTESTEP study is the incidence of postoperative incisional hernia (IH), a topic with limited existing research. Studies on TU-LESS indicate an IH incidence of 5–7%, rising to 1–30% in obese patients [56, 57]. However, these findings cannot be directly applied to vNOTES due to anatomical differences in surgical access points. Given its incision site, vNOTES may theoretically reduce IH rates in obese patients, but clinical evidence is needed to substantiate this hypothesis.

Low postoperative pain is one of the advantages of vNOTES. Up to 80% of patients undergoing conventional laparoscopic surgery report certain levels of pain that requires analgesia. The origins of post-laparoscopic pain are multifactorial, including inflammatory responses linked to surgical trauma and incision sites, as well as structural and biochemical changes in the peritoneum and diaphragm induced by pneumoperitoneum. The latter mechanism results from irritation, mechanical stretching, and foreign body stimulation, which can trigger phrenic nerve dysfunction and lead to subsequent shoulder-tip pain [58]. Since the surgical incision in vNOTES is primarily located at the posterior vaginal fornix, an area with relatively sparse nerve distribution, vNOTES theoretically outperformed TU-LESS in reducing postoperative pain. Consistently, numerous retrospective studies have demonstrated significantly lower postoperative VAS pain scores in vNOTES compared to TU-LESS or MPL [17, 31, 43–45, 59, 60]. However, high-quality evidence from RCTs remains limited.

The steep learning curve of vNOTES has also been cited as a barrier to its adoption.9 However, it was reported that with adequate training and experience, the surgical setup time can be reduced in most cases. Additionally, vNOTES may offer advantages over TU-LESS in obese patients, as evidenced by a case report describing its successful application in cholecystectomy for a morbidly obese patient [61]. 

Technological advancements have significantly enhanced the feasibility and efficiency of vNOTES. Innovations such as prone-position vNOTES for posterior uterine wall myomectomy [62], robot assisted vNOTES [63, 64], as well as the growing compatibility between vNOTES and TU-LESS instrumentation, continue to refine the technique. As TU-LESS technology progresses, parallel advancements in vNOTES are expected, potentially overcoming existing technical limitations.

Despite these advantages, there remain concerns regarding the impact of vNOTES on reproductive outcomes. Given the transvaginal access route, potential alterations in vaginal elasticity, microbial environment, and long-term pelvic floor function should be considered. Additionally, vNOTES could introduce theoretical risks of adhesion formation due to peritoneal exposure, though existing studies have yet to establish a definitive association. Further research is necessary to delineate these potential risks and to confirm whether vNOTES remains a preferable option for patients desiring future fertility.

Economic considerations are another critical factor influencing the adoption of vNOTES. While vNOTES provides superior cosmetic results and potentially lower postoperative pain, its cost-effectiveness compared to TU-LESS remains a point of debate. The high initial cost of specialized instrumentation and training requirements may deter widespread implementation, particularly in resource-limited settings. Future cost-effectiveness analyses incorporating long-term patient outcomes and healthcare expenditures will be essential for assessing the broader viability of vNOTES in clinical practice.

Furthermore, public perception and patient acceptability play a pivotal role in determining the clinical adoption of novel surgical techniques. Cultural factors and varying levels of awareness about vNOTES may impact on patients’ willingness to undergo this procedure. Studies have indicated that patient education and preoperative counseling significantly influence decision-making, and further efforts should be directed toward enhancing patient understanding of vNOTES’ benefits and potential risks.

Some previous RCTs comparing vNOTES and TU-LESS in treating gynecologic diseases either did not implement blinding or used non-therapeutic incisions for blinding. However, the later approach is controversial, as non-therapeutic incisions may harm patient welfare and introduce ethical concerns [24, 47]. Additionally, such extraneous incisions could create a confounding effect on aesthetic and postoperative pain assessments, potentially influencing the evaluation of postoperative outcomes for vNOTES and TU-LESS. Although we did not plan to inform patients of the surgical procedure which they will undergo either preoperatively or postoperatively to achieve blinding as much as possible, we acknowledge that due to the visibility of the umbilical incision, which can be easily detected by the patient, the effectiveness of blinding may be compromised. After careful consideration, we believe that the current single-blind design in our study strikes an acceptable balance between the effectiveness of blinding and patient welfare.

A notable limitation of the study is its single-center design and focus on a regional Chinese population, which may affect generalizability. Moreover, restricting the study to TU-LESS and vNOTES, without including other surgical techniques, may limit the applicability of the results. We also acknowledge that the sample size may be insufficient to detect rare complications, therefore a prospective study on the vNOTES and TU-LESS’ surgical outcomes in treating ectopic tubal pregnancy with larger sample size is warranted. Nonetheless, this two-arm, prospective RCT with an extensive long-term follow-up plan offers a valuable opportunity to refine vNOTES protocols, inform clinical guidelines, and improve patient acceptance of this minimally invasive approach.

In conclusion, the vNOTESTEP study is designed to generate high-quality evidence from an RCT on the perioperative and long-term outcomes of vNOTES in treating tubal ectopic pregnancy, with a particular focus on sexual function, pregnancy outcomes, vaginal delivery, and the incidence of incisional hernia.

## Data Availability

No datasets were generated or analysed during the current study.

## Abbreviations

BIQ: Body Image Questionnaire
BMI: Body mass index
CC: Cohort Coordinator
CM: Cohort Manager
CT: Computer Tomography
CWCCH: Chengdu Women’s and Children’s Central Hospital
FSFI: Female Sexual Function Index
GEE: Generalized estimating equations
HALON: Hysterectomy by transabdominal laparoscopy or natural orifice transluminal endoscopic surgery
HIS: Hospital Information System
IH: Incisional Hernia
MIS: Minimally Invasive Surgery
MPL: Multiport Laparoscopic Surgery
MRI: Magnetic Resonance Imaging
NOTABLE: Transvaginal natural orifice transluminal endoscopic surgery (vNOTES) adnexectomy for benign pathology compared with laparoscopic excision
OA: Outcome Assessors
PDQ: Pregnancy and Delivery Questionnaire
PROMs: Patient Reported Outcome Measures
RCT: Randomized Control Rial
TU-LESS: Transumbilical Laparoscopic Single Site Surgery
VAS: Visual Analog Scale
vNOTES: Transvaginal Natural Orifice Transluminal Endoscopic Surgery
vNOTESTEP: Transvaginal Natural Orifice Transluminal Endoscopic Surgery in Treating Ectopic Pregnancy cohort study
